## Abstract

**Aims:**

Patients with persistent atrial fibrillation (AF) and heart failure (HF) have compromised clinical outcomes. Contemporary management includes rhythm control with AF ablation, or rate control and regularization with conduction system pacing and atrioventricular nodal ablation (CSP + AVNA). These strategies have never been compared in a randomized clinical trial. The study aims to determine whether CSP + AVNA is superior to AF ablation for reducing all-cause mortality and cardiovascular hospitalization, and noninferior with respect to all-cause mortality and heart failure hospitalization.

**Methods and results:**

ABACUS is a multicentre, investigator-initiated, randomized controlled trial enrolling 220 patients with persistent AF and HF, aged >60 years, who are eligible for both treatment modalities, with at most one previous AF ablation procedure. Participants will be randomized 1:1 to either catheter ablation of AF (with pulmonary vein isolation using any routine technique) or to CSP + AVNA. All patients will undergo at least one year of follow-up. The co-primary endpoints will be tested sequentially. A number of predefined secondary endpoints, including costs, will also be evaluated.

**Discussion:**

ABACUS compares CSP + AVNA with AF ablation in patients with persistent AF and HF. The results will provide evidence to improve care in this vulnerable patient population.

## Introduction

Atrial fibrillation (AF) impacts heart function by loss of atrial contractile function, induction of tachycardiomyopathy, and deterioration of cardiac pump function due to irregular and often short cycles.^1–5^ The coexistence of persistent AF with heart failure (HF) confers an adverse prognosis.^6^

A number of strategies have been studied for treating HF patients with AF, and are summarized in *Table 1*. Maintenance of sinus rhythm by antiarrhythmic drugs has not been shown to be superior to pharmacological rate control.^9,11,30^ Catheter ablation of AF with pulmonary vein isolation (PVI) is well established^31^ and has been shown to be superior in terms of clinical endpoints as compared to medical rate or rhythm control,^12,14,16,20,22^ although some trials were negative.^15,22^ However, all these trials were performed before the era of pulsed field ablation (PFA), which has been shown to be safe and effective, although data in the HF population with persistent AF are still sparse, with 1-year recurrence rates of atrial arrhythmias of about 35%.^32^

**Table 1 oeag007-T1:** Randomized trials for treating atrial fibrillation in patients with heart failure comparing different treatment strategies

Comparison	Drug rate control	Drug rhythm control	AVNA + RVP	AVNA + BiV
Drug rhythm control	AFFIRM^7^		AIRCRAFT^8^	-
	AF-CHF^9^		Brignole 1998^10^	
	RACE^11^			
AF ablation	CAMTAF^12^		-	PABA-CHF^13^
	CASTLE-AF^14^			
	AMICA^15^	AATAC^16^		
	CAMERA-MRI^17^	AMICA^15^		
	ARC-HF^18^	CASTLE-AF^14^		
	MacDonald et al^19^	CASTLE-HTx^20^		
	CABANA^21^			
	RAFT-AF^22^			
AVNA + BiV	APAF-CRT^23,24^	-	APAF^25^	
			PAVE^26^	
			Brignole 2005^27^	
			AVAIL CLS/CRT^28^	
AVNA + HBP	-	-	-	ALTERNATIVE-AF^29^

Abbreviations: AF, atrial fibrillation; AVNA, atrioventricular nodal ablation; BiV, biventricular pacing; HBP, His bundle pacing; RVP, right ventricular pacing.

Another approach is ‘pace and ablate’ for which atrioventricular nodal ablation (AVNA) combined with right ventricular pacing (RVP) or biventricular pacing (BiVP) has been found to be superior to pharmacological therapy in patients with permanent AF with HF or AF symptoms.^8,10,23,24^ For this strategy, BiVP has been shown to provide better outcomes than RVP.^25,26^ Ablate and pace has been tested across the spectrum of left ventricular systolic function with an average left ventricular ejection fraction (LVEF) of approximately 40% in the APAF and APAF-CRT trials.^23,25^ More recently, conduction system pacing (CSP) with either His bundle pacing (HBP) or left bundle branch area pacing (LBBAP) have emerged as being more physiological alternatives to these standard pacing modalities.^33–36^ A small crossover study on AVNA randomized HBP against BiVP in patients with a narrow QRS or right bundle branch block and found superior left ventricular ejection fraction (LVEF) with HBP.^29^

The only study that randomized PVI against a ‘pace and ablate’ strategy utilized BiVP and showed that PVI was superior in terms of combined soft endpoints (LVEF, distance on the 6-minute walk test, and quality of life).^13^ However, only about half of the population had persistent AF, with an average heart rate of 80bpm and QRS width of 90 ms (and it is known that BiVP can be detrimental in patients with a narrow QRS and heart failure.^37^)

There are currently no trials which have randomized PVI against a ‘pace and ablate’ strategy with CSP in patients with persistent AF and HF. Both strategies have their advantages and limitations. Restoring and maintaining sinus rhythm by catheter ablation can improve HF due to regularization of cardiac rhythm and the restoration of atrial contractile function. However, atrial contractile dysfunction may persist in scarred atria (in which ablation results in further fibrosis). Furthermore, recurrence rates with radiofrequency ablation are high at approximately 50% at 12–18 months^38,39^ and the procedure is associated with risks as well as with significant costs. A ‘pace and ablate’ strategy is a simpler alternative which can improve HF by reversing tachycardiomyopathy, regularizing cardiac rhythm, and eliminating the need for rate-slowing drugs which may have a detrimental effect on cardiac function. However, it usually condemns the patient to AF with loss of atrial contractile function and physiological rate response (although it has been reported that 13% of patients with AF since >6 months revert spontaneously to sinus rhythm after AVNA with CSP^40^) and results in pacemaker dependency (although most patients retain an escape rhythm.^41^)

The increasing prevalence of persistent AF and HF is a challenge to the healthcare system to meet the demand for treatment, both in terms of work burden as well as cost. As previously mentioned, both PVI and ‘pace and ablate’ have been shown to be superior to pharmacological treatment, but it is ill-defined whether one of these two modalities is superior. The clinical conundrum is also present in patients who have undergone one previous attempt at PVI and in whom AF has recurred, in whom a repeat ablation needs to be weighed against a ‘pace and ablate’ option. Therefore, there is a need to compare these interventions head-to-head in their contemporary form to better define treatment strategies in this patient population.

## Methods

### Objectives

The study has two primary goals: to show that the CSP + AVNA strategy is (i) superior to AF ablation in terms of reducing all-cause mortality and cardiovascular hospitalization (CVH), and (ii) noninferior with respect to all-cause mortality and heart failure hospitalization (HFH).

### Study description

The ABACUS trial is an investigator-initiated, international, multicentric, randomized, controlled, and open-label, two-arm comparative clinical trial. It is a head-to-head comparison of AF ablation (the control arm) to CSP + AVNA in patients with persistent AF and HF who are considered eligible for both treatments. Due to the nature of the interventions, it is not possible to blind patients and primary investigators.

The trial was designed by a steering committee composed of experts in the fields of AF, cardiac pacing, catheter ablation, and HF, as well as a biostatistician ([name]) and a patient representative ([name]). The trial is conducted in academic hospitals in the following 14 countries across Europe in 30 centres (with a maximum of four centres per country to provide geographical balance): Austria, Belgium, Bulgaria, the Czech Republic, Finland, France, Germany, Hungary, Italy, Poland, Spain, Switzerland, the Netherlands, and the UK. The sponsor is the University Hospital of Geneva, Switzerland, and the trial is funded by the Swiss National Science Foundation (https://data.snf.ch/grants/grant/220116) and the GeCOR Research Foundation of the Department of Cardiology at the University Hospital (https://cardiologie-universitaire-geneve.ch/).

Logistical support and monitoring are conducted by the Clinical Research Organization (PRODUCT—project development consulting, Sofia, Bulgaria). The database is managed by the Clinical Trial Unit of the University Hospital Geneva.

The study has been registered on www.clinicaltrials.gov under the number NCT06207383, in the ISRCTN registry under number ISRCTN65526476, and on the Swiss National Clinical Trial Portal under number SNCTP000006064.

This study is conducted in compliance with the Declaration of Helsinki, the ICH-GCP as well as other locally relevant legal and regulatory requirements.

#### Patient population

Consecutive subjects who are eligible for the standard treatment of catheter ablation of persistent AF will be considered for inclusion in the trial. Inclusion and exclusion criteria are listed in *Table 2*. Patients who are considered poor candidates in routine clinical practise for one of the treatment modalities (e.g. persistant AF for several years with a severely dilated left atrium who are unlikely to benefit from AF ablation) or who are unsuitable for one of the therapies (e.g. tricuspid valve prosthesis, which contraindicates CSP) will not be included.

**Table 2 oeag007-T2:** Inclusion and exclusion criteria for the ABACUS trial

**Inclusion criteria**
Subjects fulfilling all of the following criteria are eligible for the investigation:
Age ≥ 60 years. Persistent AF with symptomatic HF despite medical therapy, considered to be suitable for AF ablation, *with at most one previous PVI procedure*. Persistent AF is defined as AF that is continuously sustained beyond seven days, including episodes terminated by cardioversion (drugs or electrical) after > 7 days.^42^ At least one prior hospital admission, or emergency room/HF clinic visit for HF in the past 2 years, with BNP > 250 pg/mL or NT-pro-BNP > 1000 pg/mL measured at any timepoint during this interval. Previous or current rate or rhythm control drug therapy. Considered eligible for CSP implantation as an alternative to AF ablation Informed Consent signed by the subject.
**Exclusion criteria**
The presence of any one of the following criteria will lead to the exclusion of the subject:
NYHA Class IV and systolic blood pressure ≤80 mmHg despite optimized therapy. Life expectancy < 2 years. Need for major surgical intervention. Myocardial infarction, stroke, or PCI within the previous 3 months. Previously implanted or planned implantation of a CRT device or pacemaker. ICD implantation without a pacing indication is acceptable. Participation in another controlled trial with active treatment. Inability to sign an informed consent form

Abbreviations: AF, atrial fibrillation; BNP, brain natriuretic peptide; CRT, cardiac resynchronization therapy; ICD, Implantable cardioverter defibrillator; HF, heart failure; NYHA, New York Heart Association; PVI, pulmonary vein isolation.

If a patient has a standard indication for an implantable cardioverter defibrillator (ICD), this is possible in both groups, but only with backup or no pacing (e.g. in case of a nontransvenous ICD) in the AF ablation group. A total of 220 patients (110 in each group) will be enrolled (see below for sample size calculation). As it is anticipated to have significant selection bias, a patient eligibility logbook will be recorded. All patients will sign an informed consent form. Each patient's follow-up begins on the day of inclusion and concludes at study closure.

#### Endpoints

##### Primary endpoints

The study has two co-primary endpoints:

The composite of all-cause death or CVH (superiority hypothesis).The composite of all-cause death of HFH (noninferiority hypothesis).

These endpoints will be evaluated sequentially in a hierarchical order, in order to preserve the type I error rate. The superiority hypothesis has to be fulfilled prior to evaluation of the noninferiority hypothesis (the former is felt to be most relevant and anticipated to be reached more readily and is therefore evaluated first). The main analysis of the primary endpoints is conducted in the full analysis population under application of the intention-to-treat principle, i.e. events are counted regardless of the implementation of the randomized ablation treatment.

The endpoint of CVH includes HFH or admission for any of the following: AF-related symptoms, stroke, acute myocardial infarction, cardiac implantable electronic device (CIED) interventions, redo procedures, or procedure-related complications. Admissions for crossover procedures are counted as CVH endpoints. AVNA during or following CSP implantation is not counted as an endpoint as it is an integral part of the strategy in patients randomized to the CSP + AVNA arm. HFH is defined as admission for worsening HF to a healthcare facility for > 24 h or unplanned hospital visits for HF requiring intravenous diuretics and/or adjustment of other medical HF therapy.

Predefined factors will be evaluated by subgroup analysis (e.g. age, sex, LVEF, heart rate, intrinsic QRS duration, NYHA class, duration of AF, history of AF ablation, etc.).

An independent Clinical Endpoints Committee will adjudicate the primary endpoints and will be blinded to treatment allocation whenever feasible.

##### Secondary endpoints

Individual components of the primary endpoints and a number of additional endpoints will be evaluated (duration of CVH, reintervention rate, crossovers, CIED implantation or upgrade, sinus rhythm at follow-up, LVEF (evaluated by echocardiography at the study centre), left atrial size, NYHA class, mEHRA score, and quality of life using the Minnesota Living with Heart Failure and EQ-5D-5L questionnaires). Patient-reported outcome measures (PROMs) at 1 year will be assessed by a visual analogue scale questionnaire developed for each study arm based upon PROMs of AF^43^ as well as for living with a pacemaker^44,45^ (see Supplementary material). Healthcare costs and cost-effectiveness will be analysed separately.

##### Safety endpoints

All cardiovascular adverse events related to pacemaker implantation, pacing, or ablation procedures will be recorded and adjudicated by an independant Clinical Endpoints Committee and an independent Data Safety and Monitoring Board.

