**Figure 1 oeag007-F1:**
[figure not shown]
Study flowchart. Abbreviations: AF, atrial fibrillation; AVN, atrioventricular node; CSP, conduction system pacing; FU, follow-up; LVEF, left ventricular ejection fraction; PVI, pulmonary vein isolation.

**Table 3 oeag007-T3:** Clinical investigation procedures and assessments

	Enrolment	Intervention (within 3 mo)	@ 6 wk^a^ (±2 wk)	@ 6 mo^a^ + each 6 mo (±2 wk)	@ 1 yr^a^ (±2 wk)	End of study visit
Consent form	X					
Randomization	X					
Medical history	X					
Medication	X	X	X	X	X	X
NYHA class	X	X	X	X	X	X
QOL	X				X	
mEHRA score	X	X	X	X	X	X
PROMs					X	
12-lead ECG	X	X	X	X	X	X
Echocardiogram (within 3 months before enrolment)	X				X	
Device check (CSP arm)		X	X	X	X	X
Adverse events		X	X	X	X	X
Mortality status		X	X	X	X	X
End visit form						X

^a^Counted from the date of intervention

Abbreviations: CSP, conduction system pacing; ECG, electrocardiogram; ICF, informed consent form; QOL, quality of life questionnaire (MLWHF + EQ-5D); PROMs, patient-reported outcome measures.

Ablation of AF may be performed according to the operator’s preference (e.g. using radiofrequency ablation, cryoablation, PFA, etc.) and following current European Heart Rhythm (EHRA) recommendations^46^ but should include PVI and restoration of sinus rhythm as goals. Additional lesions (e.g. lines, substrate modification, vein of Marshal ethanol infusion, etc.) may be performed according to the discretion of the operator. Rate and/or rhythm control medical therapy, anticoagulation, and heart failure treatment may be continued after the ablation procedure, as indicated. Operators must have performed >200 AF ablations as a primary operator.

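### The safety endpoint covers only cardiovascular adverse events, so non-fatal, non-cardiovascular procedural harm without a separate admission falls outside it and its adjudication

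*Protocol article*

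**What the plan says.** Three places in the protocol article bear on which procedural harms count.

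- **Safety endpoints.** This section is one sentence. It begins "All cardiovascular adverse events related to pacemaker implantation, pacing, or ablation procedures will be recorded and adjudicated" and names as adjudicators an independent "Clinical Endpoints Committee and an independent Data Safety and Monitoring Board". An event has to be both cardiovascular and related to implantation, pacing or ablation.
- **Primary endpoints.** Cardiovascular hospitalization (CVH) covers heart failure hospitalization and admission for several other reasons. The list ends with "cardiac implantable electronic device (CIED) interventions, redo procedures, or procedure-related complications". No organ system is named for the complications. Death is all-cause in both co-primary composites. On adjudication the section says: "An independent Clinical Endpoints Committee will adjudicate the primary endpoints and will be blinded to treatment allocation whenever feasible".
- **Table 3, visit schedule.** A row headed "Adverse events", with no qualifier, is marked at the intervention and at every later visit.

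The Secondary endpoints section adds the individual components of the primary endpoints, along with the reintervention rate and device implantation or upgrade. It lists no separate outcome for procedural complications. In describing catheter ablation of AF, the Introduction notes that "the procedure is associated with risks as well as with significant costs", so procedural risk is part of the case for the trial.

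**The concern.** Both arms are invasive, but in different ways. One is left atrial ablation with any routine energy source; the other is lead implantation plus atrioventricular nodal ablation. Some of the harms that separate them are not cardiovascular on a plain reading: pneumothorax, phrenic nerve or oesophageal injury, sedation events, kidney injury. There is no reason to expect these to be equal in kind or number in the two arms. A safety comparison limited to cardiovascular events therefore leaves out part of what a reader would want to know when choosing between the strategies.

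The limit is stated in the text, so it is not a detail that the article merely leaves to a longer document. It also differs from the scope of the primary endpoint and of the visit schedule, although the same committee adjudicates both the primary and the safety events.

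**Working it through.** No figure in the plan bears on this point, and the article gives no complication rates, so there is nothing to recompute. The sample size rests on the event rates of the two composites and does not depend on the scope of the safety endpoint. The check is to follow each type of procedure-related event through the three places above.

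| Procedure-related event | Safety endpoint | Primary endpoints | Adverse event row of Table 3 | Stated adjudication |
|---|---|---|---|---|
| Cardiovascular, any outcome | Yes | If it causes death or a qualifying admission | Yes | Yes |
| Non-cardiovascular, fatal | No | Yes, all-cause death (both composites) | Yes | Yes, as a primary event |
| Non-cardiovascular, non-fatal, separate admission | No | Yes, CVH (first composite) | Yes | Yes, as a primary event |
| Non-cardiovascular, non-fatal, no separate admission | **No** | **No** | Yes | **None stated** |

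Reasoning by row:

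1. Row 1 is the case that the Safety endpoints section is written for.
2. Row 2 is caught because death is all-cause, and the committee adjudicates the primary endpoints.
3. Row 3 is caught because the CVH definition sets no organ limit on complications. The same event, for instance a readmission for pneumothorax, is then a primary endpoint event but not a safety event.
4. Row 4 is the gap. The CVH definition counts admission for a complication. A complication that arises during the index stay, when the patient is already in hospital, is not plainly an admission for it, and one managed as an outpatient is not an admission at all. Table 3 can collect the event, but no section makes it an endpoint or sends it for adjudication. The reintervention rate would pick it up only if a reintervention followed.

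Rows 2 and 3 show that the gap is only part of non-cardiovascular harm. Row 4 shows that it is not empty, and it includes complications at the procedure itself.

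The boundary is also not sharp. The article defines neither a cardiovascular adverse event nor a procedure-related complication. A pocket infection, for example, could be read as belonging to either side of the line.

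**The case against.** The strongest reply has three parts.

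- **The serious harms are already covered.** Non-cardiovascular procedural harm that causes admission or death is adjudicated and compared between the arms through the primary endpoints and their components. This stands, and it limits the point to row 4 of the table.
- **An efficacy composite and a safety endpoint may differ in scope.** They may. A difference alone is not a contradiction, and ambiguous wording is a fairer description. But the narrower scope here belongs to the safety endpoint, where completeness matters most, and no reason for it is given.
- **This is a condensed article.** Definitions of adverse events, causality rules and reporting duties usually sit in the full protocol, and the trial commits itself to ICH-GCP. This also stands: the absence of such detail is no finding. The word that limits the endpoint is present, however, and it is all that the point rests on.

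A reader might infer more than the article supports:

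- *That non-cardiovascular harms go unrecorded.* The unrestricted row in Table 3 speaks against this. The Safety endpoints sentence says which events form the endpoint; it does not say that other events are not collected.
- *That unblinded site staff filter events through their judgement of relatedness.* The trial is open-label, but no section says who first judges relatedness or that this decides what is recorded.
- *That the data safety board sees only cardiovascular events.* The statistical section speaks of safety data in general and does not tie the board to the safety endpoint.

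**Conclusion.** The point holds in a limited form. As worded, the safety endpoint and its stated adjudication leave out procedure-related or pacing-related events that are non-cardiovascular, non-fatal and without a separate admission. The scope also does not match that of the CVH definition or of Table 3.

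The size cannot be given: the article reports no complication rates, and any share of total harm would be an invented figure. The direction of any imbalance between the arms is unknown too. The primary analyses, the power and the conduct of visits are not affected.

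The conclusion assumes that cardiovascular is meant in its plain sense, and that a complication during the index stay does not count as an admission for that complication. If the full protocol defines either term more widely, the gap shrinks accordingly. This is an inexpensive improvement to the safety comparison rather than a flaw that threatens the trial.

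**What to change.** Reword the Safety endpoints section so that it covers all adverse events related or possibly related to device implantation, pacing, atrioventricular nodal ablation or AF ablation, of any organ system. Cardiovascular events can remain as a named subset, so that nothing now planned is lost. Use a single definition of procedure-related complication in the Primary endpoints and Safety endpoints sections, and say whether a complication arising in the index stay counts towards CVH.

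The cost is a change of wording, possibly one field on the case report form, and a modest number of extra events for the committee to adjudicate in 220 patients. No new visit or procedure is needed, because Table 3 already provides for adverse events at the intervention and at each later visit. The sample size does not change.
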